#### Analyses of California Healthy Kids Survey Data

The CHKS is representative of in-school youth attending public schools within the target communities of the C2H and control programs (86 per every 100 youth, 86%, participates at study site schools). We estimate that we will have 6 intervention and 6 control schools who participate in both baseline and 24-month follow-up, each with 500 students on average. Difference-in-differences hierarchical models will be used to estimate the impact of the C2H program on primary and secondary outcomes, relative to control program communities, controlling for confounders and accounting for clustering at the school level. If statistical power allows, we will assess for modification due to gender, LGBTQ+ identity, race or ethnicity, implementation quality, and program site. Sensitivity analyses will be conducted to assess the variability of effects due to any potential violations of the parallel trend assumption and bias due to potential uneven inclusion across intervention and control schools.

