### Intervention Sites

Each of the 11 C2H intervention sites defined the geography of the implementation community by a target zip code and a high school within the target zip code. Of the 11 implementation communities, 8 communities served predominantly non-English speaking populations, 8 communities served communities where the majority of the residents were marginalized racial or ethnic minorities, 3 communities served rural communities, 6 communities served communities with incomes below the federal poverty line, and 2 communities focused on serving gender and sexual minorities. Participating communities were located across northern, central, and southern regions of California (Figure 1). Each site began a new cycle of C2H implementation between mid-2021 and 2022, after baseline data collection.

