### California Healthy Kids Survey Data–Community-Level Youth Sample

#### Collecting and Accessing Data From the California Healthy Kids Survey

This study also used the California Healthy Kids Survey (CHKS) as a mechanism for collecting evaluation data. CHKS collects school-climate data from in-school youth attending public high schools across California. Researchers and Local Educational Agencies are able to develop and build custom data collection modules as part of the CHKS system. In summer 2021, the research team developed a custom module focused on SV prevention to be included in CHKS, which was made up of an abbreviated set of measures used in the SN data collection, and WestEd integrated it into their survey system. Before and during the 2021 to 2022 and 2022 to 2023 academic years (timing guided by SN data collection for each C2H or control group) and with guidance from WestEd, the research team conducted school recruitment by contacting school district leaders and school principals from schools in the targeted zip codes of study communities via email and telephone on multiple occasions with a description of the research and incentives for schools (US $300 gift card, fees covered). For schools or districts that responded, we conducted an informational call about the purpose of the module, the risks and benefits to the school, and implementation logistics, including that implementation of the module would be requested again in 2 years. We then coordinated with WestEd to ensure the opted-in schools received the module, and schools scheduled a date for implementation. Voluntary opt-out parental consent that included specific language about the SV module was obtained by providing informed consent to students’ parents via school parent portals or websites before implementation, per WestEd protocols. Schools implemented the CHKS core and optional SV modules during one class period with all 9th- and 11th-grade students, which took about 50 minutes. Informed assent and data were collected via an online survey that was administered by teachers and/or school staff with training and protocols provided by WestEd. Students received no incentives for participation. The survey was anonymous and did not collect identifying information from students. A data use agreement with the research team’s institutions, WestEd and the California Department of Education, guided the secure transfer of data from the relevant school years to the research team, and are stored on a protected and secure server.

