
#### Follow-Up CHKS Data Collection

All schools that participated in baseline CHKS data collection in 2021‐2022 or 2022‐2023 were recruited for 24-month follow-up CHKS data collection in the academic year that included the 24-month follow-up period for each specific study community. Similar recruitment methods to those used in baseline recruitment were used, as many of the administrators have changed over the two years. Implementation, informed consent, and data transfers under new data use agreements were also conducted in the same way as baseline.

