#### LGBTQ+-Targeted Forms of SV and DV

A measure to assess experiences with forms of SV and DV targeting LGBTQ+ youth was developed by the research team. Survey participants who selected an LGBTQ+ sexual and/or gender identity received a module (via skip patterns) that contained items assessing forms of violence targeting LGBTQ+ youth, and those selecting an expansive gender identity (ie, any gender except cisgender boy or girl) received an additional set of items assessing forms of violence targeting gender expansive youth. Items included in these assessments were adapted from two existing scales developed for adults: the Identity Abuse Scale [43] and the Transgender-Specific Intimate Partner Violence Scale [44]. They were reviewed by both practice and research experts on this topic and pilot tested with LGBTQ+ youth.

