## Discussion

### Hypothesized Main Results

We hypothesize that this study will yield evidence that suggests the C2H model had modest but significant effects on reducing past 12-month prevalence of SV and DV, including sexual assault, in-person and online sexual harassment, and DV, among this sample of youth at 24-month follow-up. Additionally, we hypothesize that the C2H model will demonstrate effects on increasing community connection and improving social norms related to SV and DV, the secondary outcomes of this evaluation. We also hypothesize that these effects will diffuse across the youth participants’ SNs and school communities. We anticipate that associations between receipt of C2H and these positive outcomes will be strongest when C2H exposure was longer, when C2H implementation completed a full cycle of the program, and among Hispanic or Latino and LGBTQ+ youth. We expect to observe effect modification across these factors because we hypothesize that high-quality, prolonged exposure to the program will have stronger effects, and because the C2H intervention was intentionally implemented to be inclusive of minoritized populations, particularly toward these two demographic groups, given the size of these populations in California, strengthening the potential impact of the model on these populations.

There are limited evidence-based community-level prevention programs for SV or DV in the United States, with most targeting individual or interpersonal-level behavior change rather than community and societal-level change [18]. While not conducted in the United States and not focused on youth, other community mobilization models addressing SV or DV in other cultural settings have been shown to have positive effects for reducing SV and DV and its risk factors [25,26]. For example, the SHARE intervention evaluated in Rakai, Uganda, was demonstrated to reduce physical and sexual DV among adult women [26]. This evaluation study’s results will add to the literature on community mobilization for addressing SV and DV by providing evidence in the United States, a cultural context in which the salience of community is less pronounced, and among youth, a critical population for preventing first incidents of SV and DV.

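### The planned CHKS test of effect modification by LGBTQ+ identity uses a subgroup that is defined after exposure and cannot be fixed at baseline, so a change in disclosure in C2H schools alone could move the interaction either way

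*Protocol article*

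**What the plan says.** Under Analyses of California Healthy Kids Survey Data, the article plans hierarchical difference-in-differences models, "controlling for confounders and accounting for clustering at the school level", and adds: "If statistical power allows, we will assess for modification due to gender, LGBTQ+ identity, race or ethnicity, implementation quality, and program site". The sensitivity analyses named there concern parallel trends and uneven inclusion of schools between arms.

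The nature of the data is set out in three places:

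- Collecting and Accessing Data From the California Healthy Kids Survey: "The survey was anonymous and did not collect identifying information from students". The survey is given "during one class period with all 9th- and 11th-grade students".
- Follow-Up CHKS Data Collection: schools that took part at baseline "were recruited for 24-month follow-up CHKS data collection in the academic year that included the 24-month follow-up period".
- Intervention Sites: "Each site began a new cycle of C2H implementation between mid-2021 and 2022, after baseline data collection". The same section says that 2 of the 11 C2H communities focused on gender and sexual minorities.

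Hypothesized Main Results expects the strongest associations among, among others, LGBTQ+ youth. Part of the reason given is that "the C2H intervention was intentionally implemented to be inclusive of minoritized populations". By contrast, the Data Safety and Monitoring Plan says that SN records are linked across time points by study identifier. Analysis of SN Data plans its own interaction analysis by LGBTQ+ identity.

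**The concern.** An effect modifier should be fixed before exposure. In CHKS it cannot be. The survey is a repeated cross-section: by follow-up the baseline 11th graders have left, the 9th graders are a new intake, and the students seen in both waves cannot be matched. Every follow-up identity answer is given after C2H has started in that community.

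A programme meant to be inclusive of LGBTQ+ youth might also make students readier to report that identity. If this happened in C2H schools and not in control schools, students would move between subgroups in one arm only. Subgroup SV rates would change without any change in violence, and the difference-in-differences interaction would absorb the shift. Neither of the named CHKS sensitivity analyses is aimed at who is in the subgroup. At stake is the article's hypothesis about LGBTQ+ youth, as far as it would be argued from the community-level data.

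**Working it through.** **The plan's own figure.** CHKS Data Statistical Power gives SV of 13.8% against 11.4% with 3,000 students per arm. The usual two-proportion formula (pooled variance under the null, two-sided 5%, 80% power) gives 3,001 per arm with no allowance for clustering, so this pair of rates reproduces. It is a whole-sample figure. The article gives none for the subgroup contrast.

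**Inputs**

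- Total SV, T = 13.8% (CHKS Data Statistical Power), held constant so that the true effect is zero.
- SV ratio, LGBTQ+ to other. The article gives no CHKS value. SN Data Statistical Power gives 27% SV overall in 791 youth, and 126 of 297 LGBTQ+ youth (42.4%). The other 494 then have (0.27 × 791 − 126)/494 = 17.7%, so R = 42.4/17.7 ≈ 2.4. Using this for CHKS is an assumption.
- LGBTQ+ share in CHKS, s: not given. Assumed 25%.
- Rise in the share in C2H schools only, d: not given. Assumed 5 points. Control schools are unchanged.
- SV risk of new disclosers, r: unknown. Taken at the non-LGBTQ+ rate, the midpoint and the LGBTQ+ rate.

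**Formulas**

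- p_N = T/[(1 − s) + sR] = 0.138/(0.75 + 0.25 × 2.4) = 10.2%
- p_L = R × p_N = 24.5%
- After the shift: p_L′ = (s·p_L + d·r)/(s + d) and p_N′ = [(1 − s)·p_N − d·r]/(1 − s − d)
- Ratio of odds ratios = [odds(p_L′)/odds(p_L)] / [odds(p_N′)/odds(p_N)]. Control schools contribute 1.

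Example, low risk: p_L′ = (0.25 × 0.2453 + 0.05 × 0.1022)/0.30 = 22.1%, and p_N′ stays at 10.2%.

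| Risk of new disclosers | LGBTQ+ SV | Other SV | Interaction (points) | Ratio of odds ratios |
|---|---|---|---|---|
| Non-LGBTQ+ rate, 10.2% | 24.5% → 22.1% (−10%) | 10.2% → 10.2% | −2.4 | 0.88 |
| Midpoint, 17.4% | 24.5% → 23.3% (−5%) | 10.2% → 9.7% (−5%) | −0.7 | 0.99 |
| LGBTQ+ rate, 24.5% | 24.5% → 24.5% | 10.2% → 9.2% (−10%) | +1.0 | 1.12 |

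Total SV in C2H schools is 13.8% before and after in every row.

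**Range.** For s of 20–30%, R of 1.8–2.4 and d of 3–10 points, the same formulas give ratios of odds ratios of 0.75–0.95 (low risk), 0.97–1.04 (midpoint) and 1.04–1.34 (LGBTQ+ rate).

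**Effect on the test.** Assume 3,000 students per arm at each wave and independent observations. Summing p(1 − p)/n over the eight arm-by-wave-by-identity cells gives a standard error for the interaction of about 3.3 points. Summing 1/[np(1 − p)] gives about 0.22 on the log-odds scale. The chance of a two-sided 5% rejection is then:

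- low risk: z = −2.4/3.3 ≈ −0.7, about 11% (about 9% on the log-odds scale)
- midpoint: z ≈ −0.2, about 5.5% (5.0%)
- LGBTQ+ rate: z ≈ 0.3, about 6% (8%)

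With a 10-point shift and low-risk disclosers it is about 24% (19%). A larger standard error would bring all of these closer to 5%.

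**The case against.** The strongest case against is that the driving event is hypothetical. No section says that C2H changes disclosure. CHKS covers whole grades, about 500 students per school, and not just C2H members. The two communities with a gender and sexual minority focus are not said to be among the six CHKS intervention schools, and a long-standing focus already present at baseline would be differenced out. The analysis is also conditional on power, and a journal article may leave composition checks to an analysis plan. All of this stands. It limits the size of the point and makes every magnitude illustrative. It does not remove the structural fact: the article chooses this modifier in the one data source where it cannot be fixed at baseline, while the linked cohort already has the same test.

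It might also be said that a changing subgroup breaks parallel trends within subgroups, and that sensitivity analyses for parallel trends are planned. A general check of that kind does not measure the LGBTQ+ share by arm and wave, which is the quantity needed.

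Three stronger readings are tempting, and the article does not support them:

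- A reader might infer that the artefact runs in the hypothesised direction. It does so only if new disclosers have clearly lower SV risk than the existing LGBTQ+ group. At the midpoint the two groups fall by nearly the same proportion and the interaction almost vanishes. At the LGBTQ+ rate it reverses.
- A reader might infer that the main CHKS estimate is biased. Moving students between subgroups leaves total SV unchanged, so the unadjusted overall effect is unaffected. Bias would arise if identity were an adjusted covariate, but the article does not list it as one.
- A reader might set the within-group falls beside the detectable whole-sample reduction. The two are not comparable, because the planned quantity is a contrast between subgroups.

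**Conclusion.** The point holds as a limit on what one conditional CHKS analysis can show. The follow-up LGBTQ+ subgroup is defined after exposure, cannot be tied to baseline identity, and no check on its composition is named. Under the assumed share of 25%, ratio of 2.4 and 5-point C2H-only shift, zero true effect yields a ratio of odds ratios of 0.88, 0.99 or 1.12, depending on a risk that the survey cannot reveal. The false-positive rate rises modestly, to between 5% and about 11%. The main damage is therefore to interpretation: a CHKS interaction in either direction, or its absence, could not be read as a difference in programme effect without knowing whether disclosure changed. Only the SN cohort allows a baseline-defined subgroup.

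**What to change.** In the CHKS analysis section:

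1. Run the same difference-in-differences model with selection of an LGBTQ+ identity as the outcome. Report the estimate and its confidence interval, with the share by arm and wave, beside any CHKS LGBTQ+ subgroup result.
2. Add bounds that assign the estimated excess share the non-LGBTQ+, mid-level and LGBTQ+ SV risk in turn, and show the interaction under each. Repeat them at the limits of the interval. With 3,000 per arm and wave, a 25% share and no clustering, the standard error of the share estimate is √(4 × 0.25 × 0.75/3000) = 1.6 points, and clustering over 12 schools would normally widen it. A null result for the share is therefore not enough on its own.
3. State that the CHKS LGBTQ+ modification result is supportive, and that the hypothesis about LGBTQ+ youth rests on the SN cohort, with identity as answered at baseline.

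The cost is plan wording and one extra model on data that the study will hold. With the main analysis scheduled for summer to fall 2026, it should be fixed before that begins. The downside is that the CHKS LGBTQ+ result no longer stands alone, and the LGBTQ+ claim then applies to programme members and their networks rather than to whole schools.

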## Results

This study was funded in September 2020 for three years and was given two additional years of funding through a competitive renewal (through September 2025). A no-cost extension was granted through September 2026. Institutional review board approval was granted in February 2021. Baseline survey data were collected on a rolling basis between October 2021 and June 2023 from 953 participants of the SN sample. Baseline data were analyzed in 2025, and results related to the SN structure are expected to be published in the fall of 2026. Follow-up survey data were collected from September 2023 to November 2025 from 746 participants. Main effect analysis will take place from summer to fall 2026. Main effect findings will be published in late 2026 or early 2027.

## Discussion

### Hypothesized Main Results

We hypothesize that this study will yield evidence that suggests the C2H model had modest but significant effects on reducing past 12-month prevalence of SV and DV, including sexual assault, in-person and online sexual harassment, and DV, among this sample of youth at 24-month follow-up. Additionally, we hypothesize that the C2H model will demonstrate effects on increasing community connection and improving social norms related to SV and DV, the secondary outcomes of this evaluation. We also hypothesize that these effects will diffuse across the youth participants’ SNs and school communities. We anticipate that associations between receipt of C2H and these positive outcomes will be strongest when C2H exposure was longer, when C2H implementation completed a full cycle of the program, and among Hispanic or Latino and LGBTQ+ youth. We expect to observe effect modification across these factors because we hypothesize that high-quality, prolonged exposure to the program will have stronger effects, and because the C2H intervention was intentionally implemented to be inclusive of minoritized populations, particularly toward these two demographic groups, given the size of these populations in California, strengthening the potential impact of the model on these populations.

There are limited evidence-based community-level prevention programs for SV or DV in the United States, with most targeting individual or interpersonal-level behavior change rather than community and societal-level change [18]. While not conducted in the United States and not focused on youth, other community mobilization models addressing SV or DV in other cultural settings have been shown to have positive effects for reducing SV and DV and its risk factors [25,26]. For example, the SHARE intervention evaluated in Rakai, Uganda, was demonstrated to reduce physical and sexual DV among adult women [26]. This evaluation study’s results will add to the literature on community mobilization for addressing SV and DV by providing evidence in the United States, a cultural context in which the salience of community is less pronounced, and among youth, a critical population for preventing first incidents of SV and DV.

### Strengths and Limitations

There are a variety of limitations to this study that should be considered with regard to interpreting results. First, random assignment of the intervention was not possible, given preselection by a funder of the intervention sites. Exchangeability between intervention and control groups was strengthened by propensity score matching of control communities and strategic selection of a comparable control program from which to recruit control participants, yet for three control sites, the quality of control group matching was limited. We will use multiple strategies to try to address limits to exchangeability in our results, including the use of a quasi-experimental analytical approach (difference-in-differences) that accounts for baseline differences and covariate adjustment to control for baseline differences between the intervention and control groups. Second, there are multiple ways in which selection bias may affect our results. For example, participants were not randomly selected and instead were eligible to be in the sample based on their choice to sign up for the program (C2H or 4-H). The types of youth who may volunteer to join such a group are likely systematically different from the youth population in California, limiting the generalizability of the findings. While findings may not be generalizable to the state, because this study is being conducted across 22 communities across all regions of the state, it does include a diverse sample of youth and communities, and likely will provide relevant findings for other diverse communities that might consider implementing C2H in the United States. Third, we may observe nonrandom loss to follow-up at the 24-month follow-up. While we have used extensive efforts to keep the sample of youth engaged and retained over this long follow-up period, we will also likely need to reduce the impact of this form of selection bias by using inverse probability of censoring weighting in our analyses. Finally, this study began during the COVID-19 pandemic, with baseline data collection and intervention initiation occurring between 2021 and 2023. While we expect the pandemic to have impacted control and intervention communities in similar ways, our ability to observe diffusion of intervention effects across SNs may be limited due to the way the pandemic may have caused disruptions to the stability of youth’s SNs between baseline and follow-up. Furthermore, implementation of the C2H model was likely disrupted by the “Great Resignation” that occurred between 2021 and 2022 in the aftermath of the COVID-19 pandemic, in which an unprecedented number of US workers quit their jobs, including prevention staff at C2H implementing organizations [59]. We would expect that the Great Resignation would have a greater impact on C2H implementation than 4-H implementation because adults facilitating C2H groups were primarily paid staff, and 4-H facilitators were more often long-term volunteers who often had children in the program. Despite these limitations in this study’s design and external factors that may have impacted implementation of the C2H program, this study uses a rigorous quasi-experimental design complemented with quasi-experimental analytic techniques to account for the real-world, practical challenges of evaluating community-level programs. Moreover, this study is strengthened by its SN sampling design and implementation in 22 diverse communities.
